### 2.7 Computerized Cognitive Remediation Therapy

This study will employ the CCRT system (Nanjing Weisi Medical Technology Co., 
Ltd., model VCRT-G, Nanjing, Jiangsu, China) from the Rehabilitation Medicine 
Department of the Second Affiliated Hospital of Xinxiang Medical University. 
Patients will receive training under the guidance of trained professional 
therapists. The hardware architecture of the CCRT system comprises a single 
server and multiple treatment terminals, while the software architecture is 
divided into three components: the frontend, backend, and an extensive database. 
The frontend is integrated with multiple therapy terminals. Upon accessing a 
terminal, therapists are presented with all available training tasks, enabling 
patients to engage directly in cognitive training activities. The backend 
functions as the central host, primarily utilized for entering general patient 
information, selecting and initiating tasks, and monitoring and reviewing task 
completion status. The database is responsible for storing all patient-related 
therapy data, thereby facilitating statistical analyses by researchers. The CCRT 
includes 6 therapeutic modules: executive function, learning and memory, 
attention, perceptual-motor skills, language, and social cognition. Treatment is 
administered sequentially through these modules in a progressive manner. During 
each session, patients undertake multiple therapeutic tasks derived from various 
exercises, with each exercise offering multiple levels of difficulty.

The CCRT system encompasses over 10 distinct therapeutic tasks. Below are 
several examples: (1) Emotion Recognition: Patients observe facial expressions in 
presented images and select the corresponding emotional label. Correct choices 
earn points, enhancing social cognition; (2) Voice Coach: Patients listen to 
audio prompts and drag the described image into a collection box. Higher accuracy 
and quantity improve scores, targeting language comprehension; (3) Whack-a-Mole: 
Patients quickly tap moles randomly appearing from holes. Faster responses yield 
higher scores, training rapid decision-making; (4) Supermarket Shopping: A 
simulated store scenario where patients follow a shopping list to locate items 
across sections, integrating executive function training; (5) Train Arrival: 
Patients adjust track switches to guide color-matched trains to correct stations, 

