refining attentional control; (6) Task Cards: Patients identify and drag cards 
matching textual instructions into a collector, boosting pattern recognition; (7) 
Memory Master: Patients memorize sequentially displayed items and recall them 
under time constraints, strengthening memory retention. The system automatically 
adjusts the current training difficulty based on indicators such as the patient’s 
accuracy rate and response time from previous cognitive training stages, thereby 
adapting to improvements in the patient’s cognitive functions. CCRT is 
administered once daily, 5 times per week, over a period of 4 weeks, culminating 
in a total of 20 sessions. Relevant studies indicate that the concurrent 
application of tDCS with cognitive training enhances task accuracy more 
effectively than when these therapies are conducted separately [43]. 
Consequently, it has been determined that in Group 1 (HD-tDCS + CCRT) will be 
administered simultaneously rather than sequentially.

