to evaluate the robustness of our findings. Line charts will be employed to 
visualize the data, offering a clear depiction of outcome value trends across 
time points. Given the repeated-measures nature of the data, we will utilize 
statistical methods suitable for this design. In addition to the mixed-effects 
models, we will explore non-parametric repeated-measures approaches where 
applicable. These methods are suitable for analyzing between-group differences at 
specific time points and changes within groups over time for both primary and 
secondary outcomes. Moreover, the Likelihood Ratio Test will be used to 
specifically assess the effect of the therapy. The Bonferroni correction will be 
employed to adjust *p*-values, addressing the issue of multiple comparisons from 
evaluations at different time points.

To further elucidate the underlying mechanisms, we will conduct correlation 
analyses to investigate the relationships between alterations in neuroimaging 
metrics, serum levels of BDNF/GDNF, and cognitive performance scores in 
participants. Additionally, we intend to utilize mediation analysis models to 
assess whether intervention-induced changes in brain activity and/or BDNF/GDNF 
levels mediate improvements in cognitive outcomes. Moreover, we will perform an 
exploratory analysis of the CCRT metrics (e.g., task accuracy, reaction time) to 
compare cognitive performance during training between the HD-tDCS + CCRT group 
(Group 1) and the CCRT group (Group 3). This analysis could clarify the immediate 
neuroenhancing potential of concurrent HD-tDCS.

A stable antipsychotic medication regimen will be required for all patients, 
requiring consistent dosing for a minimum of two weeks prior to the trial and 
maintaining this regimen unchanged throughout the study period. This protocol 
will be implemented to minimize confounding effects on clinical outcomes, in 
accordance with recommendations from previous literature [52]. The Defined Daily 
Dose (DDD) methodology will be utilized to standardize antipsychotic medication 
doses across study groups. This involves converting administered doses into DDD 
units following randomization to ensure pharmacological equivalence. To account 
for dosing variability and maintain the accuracy of results, DDD values will be 
incorporated as a covariate in all statistical models. All collected data will be 

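### In-training accuracy and reaction time can hide a stimulation effect, because the training software sets difficulty from those same two indicators

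*Protocol article*

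**What the plan says.** Section 2.11 (Statistical Analysis Plan) announces an "exploratory analysis of the CCRT metrics (e.g., task accuracy, reaction time) to" set Group 1 (stimulation plus training) against Group 3 (training alone) while they train. The stated purpose is to clarify whether stimulation given during training enhances performance at once. Accuracy and reaction time are the only metrics named, as examples.

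Section 2.7 (Computerized Cognitive Remediation Therapy) describes the device that produces them. Training draws on exercises, each "exercise offering multiple levels of difficulty". The software "adjusts the current training difficulty based on indicators such as" accuracy and response time in earlier stages, so that difficulty follows the patient's improvement; this adjustment is automatic. In Group 1 the two therapies are "administered simultaneously rather than sequentially", so stimulation can act on the performance that drives the adjustment. The section also says that a database stores the patients' therapy data for statistical use.

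The article does not say that difficulty is held fixed or equal for this comparison, nor that the level reached is an outcome.

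**The concern.** The two metrics named for the comparison are the two inputs of the rule that sets difficulty. If stimulation helps, a Group 1 patient performs better, is given harder items, and accuracy is drawn back towards whatever success rate the rule aims at. Reaction time is then recorded on harder items than in Group 3. Difficulty is a post-randomisation variable that responds to the effect being measured, so accuracy and reaction time are not on a common scale across the two groups.

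At stake is the only stated analysis of performance during stimulation. A null or unfavourable result could be read as evidence against enhancement during concurrent delivery, which is the reason section 2.7 gives for delivering the therapies together, when it may only reflect the adaptive software.

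**Working it through.** The plan gives no figure for this analysis, so there is none to reproduce. From the documents come the contrast, the two metrics, the indicators behind the adjustment, 20 sessions and 12 patients per group. Everything else below is an assumption, because the adaptation rule is not described.

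**1. Why accuracy can lose the gain.** Let the probability of a correct answer be logistic(θ − d), with ability θ and difficulty d. If the rule settles at a target success rate p*, then d = θ − logit(p*). Accuracy equals p* in both groups whatever their ability, and the difference in d equals the difference in θ. For a rule of up after two correct and down after one wrong, balance requires p² = 1 − p², so p* = √0.5 = 0.707.

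**2. Check by simulation of that rule.** Inputs: 6,000 patients per arm, 900 trials with the first 300 discarded, step 0.2 logit, true gain 0.5 SD.
- Adaptive: accuracy 70.6% in both arms (difference 0.04 SD); level reached differs by 0.51 SD.
- Fixed difficulty: 50.4% vs 60.2% (0.48 SD).
- With a gain of 1.0 SD: accuracy difference 0.00 SD, level difference 0.99 SD.

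**3. Second simulation, block-wise rule.** Inputs: 20 sessions, 20,000 patients per arm, difficulty up at 80% correct or more and down below 60%, true gain 0.5 SD. Entries are Group 1 minus Group 3 in SD units for sessions 6 to 20; positive reaction time means slower.

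| Assumption | Accuracy | Reaction time | Level reached |
|---|---|---|---|
| Fixed difficulty | +0.45 | −0.48 | equal by construction |
| Fast adaptation | −0.01 | +0.02 | +0.50 |
| Fast, harder levels intrinsically slower | 0.00 | +0.48 | +0.49 |
| Difficulty ceiling | +0.30 | −0.29 | +0.46 |
| Slow adaptation (step 0.05) | +0.44 | −0.39 | +0.50 |

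**4. When reaction time changes sign.** Let log RT = a − b(θ − d) + c·d. After settling, θ − d is the same in both groups, so the group difference is c times the difference in d. With c = 0 it vanishes. With the assumed c = 0.15 and mean levels 0.108 vs −0.389, it is 0.15 × 0.497 = 0.075, a ratio of e^0.075 = 1.08. The simulated means agree: 615.8 / 571.5 = 1.08. Reversal therefore needs the extra assumption c > 0.

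**5. Dependence on the sessions used.** In session 1 under fast adaptation the accuracy difference is still 0.48 SD, although levels already differ by 0.44 SD because the rule acts within the session. Over all 20 sessions, accuracy is 68.5% vs 68.2%, a gap of 0.3 points, against 87.3% vs 81.7%, or 5.6 points, at fixed difficulty. In SD units the 0.3 points is still 0.39, because adaptation also narrows the spread between patients (0.003 / 0.39 ≈ 0.008, against 0.056 / 0.46 ≈ 0.12). The early climb thus leaves a trace in accuracy, small in absolute terms.

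**The case against.** The strongest case on the other side has four parts.

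- **The rule is unknown.** Section 2.7 speaks of previous training stages and of modules worked through in sequence, which suggests stage-wise, lagged adjustment. Convergence on every task within 20 sessions is not established, and the analysis is aimed at an immediate effect, where early sessions matter most. This stands. A reader might infer that a real gain will be hidden or reversed in this trial. The documents do not support that: slow adaptation or a ceiling only attenuates the gain, and reversal appears only for reaction time, under an added assumption.
- **The metrics are examples and the article is condensed.** The list does not exclude level reached, and no model is given. This stands in part: it would be wrong to say that the plan rules out handling difficulty. But the point is not an omission. The article names two metrics and a mechanistic reading that conflict with its own account of the software.
- **The analysis is exploratory and the claim hedged.** CCRT metrics are not among the outcomes in section 2.9, Table 1 or Table 2. This stands and limits the severity. A reader might infer that the main result is compromised. It is not: the MCCB and the HD-tDCS × CCRT interaction do not use these metrics.
- **Power is low in any case.** For a 0.5 SD difference with 12 per group, a normal approximation gives Φ(0.5 × √(12/2) − 1.96) = Φ(−0.735) = 0.23; a t-test gives about 22%. A null is likely with any metric, although a repeated-measures model may do better. That is a reason not to lose further signal, and it does not remove the bias.

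**Conclusion.** The point holds as a risk of misreading. Comparing Group 1 with Group 3 on accuracy and reaction time from adaptive training can attenuate or hide a real gain, and can make reaction time look worse if harder levels are intrinsically slower. For an assumed true gain of 0.5 SD, the accuracy difference after the early sessions ranges from about 0 SD (fast adaptation) through about 0.3 SD (ceiling) to about 0.4 SD (slow adaptation). Level reached keeps 0.46 to 0.51 SD in every adaptive scenario. These figures rest on assumed rules and logistic items; the direction of the problem follows from the design described in section 2.7. Severity is minor to moderate, because the analysis is exploratory and the primary MCCB analysis is unaffected.

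**What to change.** In section 2.11, name the difficulty level reached, per task and session, as the main metric for Group 1 vs Group 3, for example its slope over the 20 sessions in a mixed model. First confirm that the system exports level logs; section 2.7 makes this likely but does not state it. Report how many patients reach the top level of a task, since a ceiling also limits this metric.

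Use accuracy and reaction time as between-group evidence only where difficulty is the same by design, such as the part of the first session before any adjustment. This requires a common starting level, which should be confirmed. Elsewhere report them descriptively.

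Matching on level, or adding it as a covariate, is not a remedy: level is itself affected by treatment, so conditioning on it can bias the comparison.

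The cost is a few sentences of analysis wording and, if logs exist, a small extra data export. Nothing in the intervention or the sample size changes.

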**Methods::**

Schizophrenia patients will be randomly assigned to one of 4 groups: HD-tDCS + CCRT group (Group 1), HD-tDCS group (Group 2), CCRT group (Group 3), and a control group (Group 4). The central electrode will be personalized using magnetic resonance imaging (MRI)-guided localization in the medial prefrontal cortex (mPFC). CCRT includes 6 therapeutic modules and 10 distinct tasks. Both HD-tDCS and CCRT will be administered once daily, 5 days per week, for 4 consecutive weeks, culminating in a total of 20 sessions. Assessments will occur at baseline (T0), after 10 sessions (T1), after 20 sessions (T2), and after 6 months of follow-up (T3). The primary outcome measure is the change in cognition. We will employ multimodal MRI, serum concentrations of brain-derived neurotrophic factor (BDNF) and glial cell line-derived neurotrophic factor (GDNF) to explore the underlying mechanisms.

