### 2.3 Randomization 

Randomization will be performed by a statistician who does not take part in the 
study. All eligible participants will be allocated into four groups using a 
computer-generated random number table. Each assigned a specific group number: 
HD-tDCS + CCRT (Group 1), HD-tDCS (Group 2), CCRT (Group 3), and control (Group 
4). For the randomization process, personnel employed Microsoft Excel 2019 
software (Microsoft Corp., Redmond, WA, USA) to enter 48 participants into a spreadsheet, assigning each a unique 
identifier ranging from “1–48”. They then used the “=RAND()” function to 
generate a random number for each assigned number. Subsequently, these random 
values were fixed using the “Paste Special” dialog box. Following this, the fixed 
random values were sorted in descending order. The sorted numbers were then 
divided into four groups, each comprising 12 numbers, resulting in a total of 48 
numbers. This procedure effectively randomized the 48 patients into four groups, 
with each group consisting of 12 individuals. Once the randomization scheme was 
established, it was secured in opaque envelopes, which were opened sequentially 
according to the order of participant enrollment. The allocation scheme within 
each envelope determined the group assignment for each patient. This method 
ensured that study personnel could not compromise the randomization process by 
having prior knowledge of the randomization scheme. The progression of 
participants through the screening, randomization, therapy, and follow-up stages 
is illustrated in Fig. 2.

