### 2.11 Statistical Analysis Plan

The sample size was calculated using G*Power software (version 3.1.9.7, 
Heinrich-Heine-Universität Düsseldorf, Düsseldorf, Germany), 
employing an F-test and a repeated-measures ANOVA model. In this study, we 
established the probability of a Type I error (α) at 0.05, the 
probability of a Type II error (β) at 0.20, and the statistical power (1 
- β) at 0.80, with an effect size (f) of 0.25. The required sample size 
was calculated to be 36 participants. Accounting for a 20% dropout rate and 
ensuring equal group sizes, the target sample size was determined to be 48 
participants, with 12 participants per group. The calculation of the sample size 
mentioned above is based on the sample size calculation methods adopted in 
previous literature [50]. An article suggests that when designing a preliminary 
study with no prior information for reference, a sample size of 12 participants 
per group is appropriate based on feasibility, improvements in the precision of 
mean and variance estimates, and regulatory considerations [51]. The 
sample size in this study satisfies the previously mentioned criteria and will 
offer enough statistical power to achieve the objectives.

We will utilize histograms and the Shapiro-Wilk test to assess the normality of 
the data distribution. For normal distribution data, continuous variables will be 
reported as mean ± standard deviation, whereas categorical data will be 
presented as frequencies (n) and percentages (%). Statistical tests such as 
one-way analysis of variance (ANOVA), Mann-Whitney U test, *t*-test, and chi-square 
test will be employed to assess baseline differences among groups. In accordance 
with the Consolidated Standards of Reporting Trials (CONSORT) guidelines, all 
analyses will be conducted using the intention-to-treat (ITT) principle, whereby 
participants will be analyzed according to their original randomization group. To 
address missing data within the ITT framework, we will employ linear 
mixed-effects models. These models are appropriate for making valid inferences 
under the missing-at-random assumption and are well-suited for managing the 
unbalanced data resulting from participant drop-out. To specifically assess the 
synergistic effect between HD-tDCS and CCRT, the models will incorporate the 
HD-tDCS × CCRT interaction as a fixed effect. We will conduct 
sensitivity analyses by comparing the results derived from mixed-effects models 

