## 3. Expected Results

This study will evaluate between-group differences at specific time points and 
within-group changes over time for both primary and secondary outcomes. We 
hypothesize that MRI-guided HD-tDCS combined with CCRT will result in more 
significant improvements compared to those receiving HD-tDCS or CCRT alone. 
Following four consecutive weeks of treatment, it is anticipated that the 
combined group will exhibit amelioration of prefrontal dysfunction, as measured 
by MRI, and demonstrate significantly elevated expression levels of BDNF and 
GDNF.

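### T0 scores are collected for MCCB and every clinical scale, but section 2.11 neither adjusts for them nor sets a common T0 mean, so group contrasts are less precise than they could be

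*Protocol article*

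**What the plan says.** Table 2 (section 2.9) lists MCCB, BPRS, PANSS, CGI, SDSS and SQLS at T0, T1, T2 and T3. Section 2.11 specifies linear mixed-effects models with an HD-tDCS × CCRT fixed effect. Its one statement on covariates is that "DDD values will be incorporated as a covariate in all statistical models". For baseline it plans significance tests between groups and nothing further.

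Section 2.11 presents its methods as suited to group differences at "specific time points and changes within groups over time for both primary and" secondary outcomes. Section 3 repeats the aim: "This study will evaluate between-group differences at specific time points". The abstract words the outcome differently: "The primary outcome measure is the change in cognition". On allocation, section 2.3 describes a randomly sorted list of 48 cut into four sets of 12 and concludes: "This procedure effectively randomized the 48 patients into four groups". It describes no stratification.

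**The concern.** The main hypothesis is that Group 1 improves more than Group 2 and more than Group 3. With 12 patients per arm, each of those contrasts needs all the precision it can get. The T0 value of an outcome is usually its strongest predictor, and here it is collected for every scale. Section 2.11 goes down to covariate level and names the antipsychotic dose, but not the T0 score.

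Two things follow. Variance that T0 could explain stays in the error term. In addition, a chance T0 gap between two arms moves the realised estimate: upwards by rho times the gap in a raw visit comparison, and in the opposite direction by (1 − rho) times the gap in a change comparison. Testing for baseline differences may detect such a gap but does not remove it.

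**Working it through.** **Inputs from the article.** Four groups of 12 and four visits (sections 2.1, 2.3 and 2.11). Section 2.11 "established the probability of a Type I error (α) at 0.05" and sets power "at 0.80, with an effect size (f) of 0.25"; the required number "was calculated to be 36 participants", raised to 48 for 20% dropout and equal groups.

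**Assumptions.** The article gives no T0-to-follow-up correlation, so rho is taken over 0.5 to 0.9. Variances are equal across visits, and complete data are assumed for the precision figures.

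**1. The plan's own figure.** Repeated-measures ANOVA, group × time interaction, k = 4 groups, m = 4 measurements, rho = 0.5 and sphericity assumed:

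- λ = f²·N·m/(1 − rho) = 0.0625 × 36 × 4/0.5 = 18
- df = (k − 1)(m − 1) = 9 and (N − k)(m − 1) = 96
- Power = 0.825. The next lower balanced N, 32, falls below 0.80.
- 36/0.8 = 45, rounded up to 48 for four equal groups.

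The figure reproduces. With three measurements (T1 to T3 only), power at N = 36 is 0.749, short of 0.80. So the calculation most naturally counts T0 as one of the repeated responses.

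**2. Chance T0 imbalance.** The SD of the difference in T0 means between two arms is √(2/12) = 0.41 SD. A gap above 0.5 SD arises in 22% of pairs. A 0.5 SD gap shifts the contrast as follows:

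| rho | raw visit difference | difference in change |
|---|---|---|
| 0.5 | 0.5 × 0.5 = +0.25 SD | −0.5 × 0.5 = −0.25 SD |
| 0.7 | 0.5 × 0.7 = +0.35 SD | −0.5 × 0.3 = −0.15 SD |

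**3. Error variance.** Relative to a raw score: raw 1, change 2(1 − rho), baseline-adjusted 1 − rho². The adjusted value is below both others for every rho between 0 and 1. The saving is rho² against raw and 1 − (1 + rho)/2 = (1 − rho)/2 against change.

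| rho | raw | change | adjusted | saved vs raw | saved vs change |
|---|---|---|---|---|---|
| 0.5 | 1.00 | 1.00 | 0.75 | 25% | 25% |
| 0.7 | 1.00 | 0.60 | 0.51 | 49% | 15% |
| 0.8 | 1.00 | 0.40 | 0.36 | 64% | 10% |
| 0.9 | 1.00 | 0.20 | 0.19 | 81% | 5% |

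A generalised least squares check of the four-group, four-visit model agrees. The SE of Group 1 vs Group 3 at T2 (raw, change, common T0 mean) is 0.408, 0.408, 0.354 at rho 0.5 and 0.408, 0.316, 0.292 at rho 0.7. These savings are before the small cost of estimating the slope on T0.

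**4. Power for one pairwise contrast.** Illustrative true difference 0.8 SD, 12 per arm, error pooled over four arms (43 df with DDD, 42 with DDD and T0), two-sided 0.05 without multiplicity correction:

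| rho | raw | change | adjusted |
|---|---|---|---|
| 0.5 | 48% | 48% | 60% |
| 0.7 | 48% | 70% | 76% |
| 0.8 | 48% | 86% | 89% |

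Using only the two arms compared and charging for the slope, the rho 0.7 row becomes 47%, 68% and 72%.

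**The case against.** The strongest reply is that section 2.11 never says DDD is the only covariate. A condensed article may leave the full model equation to an analysis plan that is not shown. That stands as a limit on the point: a reader might infer that baseline adjustment has been ruled out, and the text does not say so. What remains is that the covariate statement covers all models and the T0 score is not in it.

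Second, T0 is probably already in use. The abstract's outcome is change, the model is a repeated-measures one, and the sample size reproduces with four measurements but not with three. This also stands. It makes the change contrast the fair comparator, so the large gains over a raw visit difference (up to 81% of variance) should not be read as the expected loss. It does not remove the point: with unconstrained group means and complete data, a group × visit model returns either the raw or the change contrast, and both have larger variance than the adjusted one.

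Third, the benefit over change fades as rho rises, to 5% of variance at rho 0.9. That is correct.

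Fourth, a reader might take the imbalance as bias. Randomisation keeps the unadjusted contrasts unbiased on average, and their standard errors already allow for chance gaps. Imbalance and lost precision are therefore largely one loss, not two defects.

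Finally, one might apply f = 0.25 to a four-group test at a single visit and quote that as the trial's power. The article attaches f to a repeated-measures F-test and names no such single-visit test.

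**Conclusion.** The point holds in a limited form. As written, section 2.11 does not use the T0 score as a covariate or set a common T0 mean, and on either reading of the model the between-group contrasts are less precise than the collected data allow. Against change from T0, the more natural reading, the avoidable error variance is 25% at rho 0.5, falling to 5% at rho 0.9. Against a raw visit difference it is 25% rising to 81%. For a 0.8 SD difference the power gain is about 12 points at rho 0.5 on either reading. At rho 0.7 it is about 7 points over change or 28 over raw.

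These sizes rest on an assumed rho, equal variances and an illustrative effect, none of which the article supplies. The documents do not support the stronger claims that DDD is fixed as the sole covariate, that the estimates are biased, or that the largest losses are certain. The point is separate from how the HD-tDCS × CCRT term is crossed with time.

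**What to change.** Keep the DDD sentence in section 2.11 and add:

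*For each outcome, the mixed model will include T0, T1, T2 and T3 as responses with the group means constrained to be equal at T0, and Group 1 vs Group 2 and Group 1 vs Group 3 will be estimated as baseline-adjusted differences at each post-baseline visit.*

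Apply it to MCCB, BPRS, PANSS, CGI, SDSS and SQLS. This version keeps every randomised patient with a T0 score, which suits the stated intention-to-treat approach and the 20% dropout allowance.

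An alternative takes T1 to T3 as responses with the T0 value and T0 value × visit as covariates. It omits patients with no post-baseline visit and uses about one degree of freedom per visit.

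The cost is one sentence, with no extra patients or data. Settling it before unblinding also closes the choice between raw and change contrasts, which a chance T0 gap pushes in opposite directions.
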